## 8.4 Severity Assessment

AEs will be graded by severity as follows (where 0 = absent, 1 = mild, 2 = moderate, 3 = severe):

| Adverse event                                    | Grade | Measurement                                                                                                  |
|--------------------------------------------------|-------|--------------------------------------------------------------------------------------------------------------|
| Tenderness or pain at intradermal injection site | 0     | No pain at all                                                                                               |
|                                                  | 1     | Painful on touch; easily tolerated                                                                           |
|                                                  | 2     | Painful when limb is moved; interferes with daily activity                                                   |
|                                                  | 3     | Severe pain at rest; prevents daily activity                                                                 |
| Redness at intradermal injection site            | 0     | 0 mm                                                                                                         |
|                                                  | 1     | 1 – 50 mm                                                                                                    |
|                                                  | 2     | 51 – 100 mm                                                                                                  |
|                                                  | 3     | > 100 mm                                                                                                     |
| Swelling at intradermal injection site           | 0     | 0 mm                                                                                                         |
|                                                  | 1     | 1 – 20 mm                                                                                                    |
|                                                  | 2     | 21 – 50 mm                                                                                                   |
|                                                  | 3     | > 50 mm                                                                                                      |
| Fever (oral)                                     | 0     | ≤37.5°C                                                                                                      |
|                                                  | 1     | 37.6 – 38.0°C                                                                                                |
|                                                  | 2     | 38.1 – 39.0°C                                                                                                |
|                                                  | 3     | >39.0°C                                                                                                      |
| Other AEs                                        | 0     | Absence of symptom                                                                                           |
|                                                  | 1     | Awareness of symptom but tolerated; transient or mild discomfort; little or no medical intervention required |
|                                                  | 2     | Discomfort enough to cause limitation of usual activity; some medical intervention or therapy required       |
|                                                  | 3     | Incapacitating, absent from work, or bed rest required; hospitalisation possible                             |

Table 5. Severity grading for AEs

## 8.5 Laboratory Assessments

All laboratory results will be reviewed and recorded in the CRF after being signed by the Investigator. A note will be made of whether each result is normal, abnormal but not clinically significant, or abnormal *and* clinically significant. In the latter case trial eligibility will be reviewed and necessary referrals or tests will be offered.

The severity of laboratory test abnormalities will be assessed according to the scale in Table 6 (adapted from (67))

| Laboratory Test                                                                        | Grade 1           | Grade 2           | Grade 3           |
|----------------------------------------------------------------------------------------|-------------------|-------------------|-------------------|
| Hb (female) – decrease from testing laboratory LLN in gm/dl                            | >1.0 - <1.5       | ≥1.5 & <2.0       | ≥2.0              |
| Hb (male) – decrease from testing laboratory LLN in gm/dl                              | ≥1.5 & <2.0       | ≥2.0 & <2.5       | ≥2.5              |
| Absolute neutrophil count (ANC, cells/mm  )                                | 1000-1499         | 500-999           | <500              |
| Leukopenia (WBC, cells/mm  )                                               | <3500 - ≥2500     | <2500 - ≥1500     | <1500             |
| Platelets (cells/mm  )                                                     | 125,000 – 135,000 | 100,000 – 124,000 | 20,000-99,000     |
| Bilirubin – when accompanied by any increase in Liver Function Test increase by factor | 1.1 – 1.25 x ULN  | 1.26 – 1.5 x ULN  | 1.51 – 1.75 x ULN |

|            |                  |                  |            |
|------------|------------------|------------------|------------|
| ALT        | 1.25 – 2.5 x ULN | >2.6 – 5.0 x ULN | >5.0 x ULN |
| Creatinine | 1.1 – 1.5 x ULN  | >1.6 – 3.0 x ULN | >3.0 x ULN |

Table 6: Severity grading criteria for clinically significant laboratory abnormalities (67)

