| Blood Sampling Schedule        | Safety blood tests (FBC, coagulation screen and clinical chemistry) as per schedule (table 1)
HIV, hepatitis B & hepatitis C antibody blood tests at screening
Exploratory immunology tests at screening, as per schedule (table 1)
HLA testing at day 0                                                                                                                                                     |
| Primary Evaluation Criteria    | Actively and passively collected data on adverse events                                                                                                                                                                                                                                                                                                                                                               |
| Secondary Evaluation Criteria  | Laboratory markers of cell mediated immunity in blood and bronchoalveolar lavage samples                                                                                                                                                                                                                                                                                                                              |

| Attendance number                               | 1  | 2   | 3   | 4    | 5   | 6   | 7   | 8    | 9   | 10  | 11  |
|-------------------------------------------------|----|-----|-----|------|-----|-----|-----|------|-----|-----|-----|
| Timeline (days)*                                | S  | 0   | 2   | 7    | 14  | 28  | 30  | 35   | 42  | 84  | 168 |
| Timeline (weeks)*                               | S  | 0   |     | 1    | 2   | 4   |     | 5    | 6   | 12  | 24  |
| Time windows (days)                             |    |     | ±1  | -2+3 | ±4  | ±5  | ±1  | -2+3 | ±4  | ±14 | ±21 |
| Inclusion/exclusion criteria                    | X  |     |     |      |     |     |     |      |     |     |     |
| Review contra-indications                       | X  | X   |     | X    |     | X   |     | X    |     |     |     |
| Informed consent                                | X  |     |     |      |     |     |     |      |     |     |     |
| Medical history                                 | X  | (X) | (X) | (X)  | (X) | (X) | (X) | (X)  | (X) | (X) | (X) |

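### Table 6 gives no grade to bilirubin above 1.75 x ULN or platelets below 20,000, although less extreme values are Grade 3; ALT and creatinine have small gaps between Grades 1 and 2

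*Protocol*

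**What the plan says.** Protocol section 8.5 fixes how laboratory results are graded: "The severity of laboratory test abnormalities will be assessed according to the scale in Table 6". Table 6 has three columns, Grades 1 to 3. Section 8.4 grades adverse events on a scale with the same top ("where 0 = absent, 1 = mild, 2 = moderate, 3 = severe"). Neither section defines a Grade 4, and nothing says how to treat a value beyond the last printed limit.

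The bilirubin row is conditional ("Bilirubin – when accompanied by any increase in Liver Function Test increase by factor"), and its Grade 3 is "1.51 – 1.75 x ULN". Grade 3 for platelets runs from 20,000 to 99,000 cells/mm³. For ALT, Grade 1 ends at 2.5 x ULN and Grade 2 begins above 2.6 x ULN. For creatinine, Grade 1 ends at 1.5 x ULN and Grade 2 begins above 1.6 x ULN.

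Safety is the primary objective (section 3), and the primary evaluation criterion in the Trial Summary is "Actively and passively collected data on adverse events".

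**The concern.** A severity scale should give every abnormal result exactly one grade, and a worse result should never rank below a milder one. Table 6 breaks this for bilirubin and platelets. Once a liver test is raised, bilirubin of 1.6 x ULN is Grade 3 but 2.0 x ULN has no grade. Platelets of 25,000 are Grade 3 but 15,000 have no grade. A listing or count built strictly from Table 6 would show the milder case as severe and leave the worse one blank.

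The ALT and creatinine gaps are narrower and sit at the boundary between mild and moderate. Section 8.6 uses that boundary when it singles out moderate or severe events still present at the end of the trial, so a result without a grade there would have to be placed by judgement.

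**Working it through.** The plan states no figure to reproduce. The check is to read each row of Table 6 as printed and ask which abnormal values receive no grade.

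| Test | Grade 1 | Grade 2 | Grade 3 | Values with no grade |
|---|---|---|---|---|
| Bilirubin (x ULN, with a liver test rise) | 1.1–1.25 | 1.26–1.5 | 1.51–1.75 | all above 1.75 |
| Platelets (thousands/mm³) | 125–135 | 100–124 | 20–99 | all below 20 |
| ALT (x ULN) | 1.25–2.5 | >2.6–5.0 | >5.0 | above 2.5, up to and including 2.6 |
| Creatinine (x ULN) | 1.1–1.5 | >1.6–3.0 | >3.0 | above 1.5, up to and including 1.6 |
| Neutrophils (cells/mm³) | 1000–1499 | 500–999 | <500 | none |
| White cells (cells/mm³) | 2500 to <3500 | 1500 to <2500 | <1500 | none |

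Both haemoglobin rows also have an open-ended Grade 3: a fall of 2.0 g/dl or more below the lower limit for women and 2.5 g/dl or more for men.

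**Closed top grade.** With the rows coded as printed, bilirubin of 1.51 and 1.75 x ULN returns Grade 3, and 1.76, 2, 3 and 10 x ULN return no grade. Platelets of 99,000 and 20,000 return Grade 3, and 19,000, 10,000 and 1,000 return no grade. With platelets reported in thousands, the only ungraded values up to 135 are 1 to 19.

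**Interior gaps.** To two decimals, the ungraded values are 2.51 to 2.60 x ULN for ALT and 1.51 to 1.60 x ULN for creatinine. Rounding to one decimal does not close the gaps: Grade 2 starts strictly above 2.6 and 1.6, so 2.6 and 1.6 themselves have no grade.

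**Width in reported units.** The protocol gives no ULN, so these ranges are assumptions.

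- ALT, ULN 35 U/L: 2.5 × 35 = 87.5 and 2.6 × 35 = 91, so 88 to 91 are ungraded (4 whole-number results).
- ALT, ULN 55 U/L: 2.5 × 55 = 137.5 and 2.6 × 55 = 143, so 138 to 143 are ungraded (6 results).
- Creatinine, ULN 80 µmol/L: 1.5 × 80 = 120 and 1.6 × 80 = 128, so 121 to 128 are ungraded (8 results).
- Creatinine, ULN 110 µmol/L: 1.5 × 110 = 165 and 1.6 × 110 = 176, so 166 to 176 are ungraded (11 results).

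**Exposure.** Table 1 schedules biochemistry at four visits after day 0 (days 2, 7, 30, 35) and haematology at two (days 7, 35). With 36 participants, that is 36 × 4 = 144 biochemistry panels and 36 × 2 = 72 blood counts. One participant is 1/12 = 8.3% of a group. That figure is the weight of a single case, not the chance that one occurs.

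**The case against.** The strongest reply is that nothing is lost in practice. Under section 8.5 every laboratory result goes into the CRF, is signed by the Investigator and is classed for clinical significance whatever its grade. Section 8.3 leaves final adverse event grading to the Investigator. If the abnormality is recorded as an adverse event, the row for other events in Table 5 has a Grade 3 without a numeric limit. Section 8.1 also allows an important medical event to be treated as serious. This stands: a reader might infer that a severe abnormality could pass unnoticed, and the documents do not support that.

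A reader might also infer that the worst results are lost in all four rows. They are not. ALT above 5.0 x ULN and creatinine above 3.0 x ULN are Grade 3; only bilirubin and platelets lose their extremes. The bilirubin example also holds only when a liver test is raised, because an isolated rise of 1.6 x ULN is not graded by this row either.

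Nor do the documents show that a missing grade would alter the safety conclusion. Section 9.1 describes no count by laboratory grade, any such table may be specified in an analysis plan that is not at hand, and the event itself would stay visible in the data.

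The reply does not remove the fault. Section 8.5 prescribes the bands themselves, so this is stated text that fails at its edges, not detail left for later. Investigator discretion fills the holes only by replacing a fixed scale with case-by-case judgement. The closed bands do not look like a convention of this protocol either: the other rows of Table 6, and redness, swelling and fever in Table 5, all have an open-ended Grade 3.

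**Conclusion.** Table 6 is wrong as written. It gives no grade to bilirubin above 1.75 x ULN (with a liver test rise) or to platelets below 20,000, although less extreme values are Grade 3. Secondarily, it skips a band 0.1 x ULN wide between Grades 1 and 2 for both ALT and creatinine.

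The point is minor. It concerns how severity is classified and tabulated, and such values should be rare because clinically significant abnormalities at screening are excluded (section 5.2). It is still worth correcting in a trial whose primary objective is safety. The conclusion rests on the printed band edges and on the absence of any higher grade in the protocol. It does not depend on the assumed ULN ranges, which only show how wide the interior gaps are, or on the published scale from which Table 6 was adapted.

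**What to change.** Reconcile Table 6 so that each row is contiguous and its top grade covers every more extreme value. One way is an open-ended Grade 3 for bilirubin and platelets, as in the table's other rows, with Grade 2 for ALT and creatinine starting where Grade 1 ends. Adding a further grade above 3 would also close the top, and the documents do not settle which was intended. Keep the liver test condition on the bilirubin row visible, so that it is clear when the row applies.

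Then apply the corrected scale to all results already graded. This version of the protocol was amended after vaccination had begun (section 4.1), so such results will exist.

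The cost is small: a few cells in Table 6, a protocol amendment under section 11.1, and a re-check of graded results. No new data are needed.

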## 8.6 Reporting Procedure for Adverse Events

Adverse events will be recorded in the CRF. Those adverse events likely to be related to the vaccine, whether serious or not, which persist at the end of the trial will be followed up by the Investigator until their complete disappearance. Moreover, any serious adverse event likely to be related to the vaccine and occurring after trial termination should be reported by the Investigator according to the procedure described below.

The outcome of any non-serious adverse event occurring within 30 days post-vaccination or any SAE reported during the entire trial will be assessed as:

- Recovered/resolved
- Not recovered/not resolved
- Recovering/resolving
- Recovered with sequelae/resolved with sequelae
- Fatal

Subjects who have moderate or severe on-going AEs at the completion of the trial will be advised to consult their General Practitioner (National Health Service) if the event is not considered to be related to the vaccine. A follow-up visit will be arranged to manage the problem and to determine the severity and duration of the event, if it is considered to be related to the vaccine. If appropriate, specialist review within the NHS will be arranged.

## 8. 7 Reporting of Serious Adverse Events

All SAEs will be documented accurately and notification deadlines respected as specified in the site-specific SOP. SAEs will be reported within 24 hours by the Investigator to the Sponsor or person with appropriate responsibility delegated from the Sponsor (Chief Investigator), and to the Local Safety Committee (see section 4.4). This will be performed by emailing an electronic version of the completed SAE Initial Report Form (CCVTM form VC004F1). Any relevant information concerning the SAE that becomes available after the SAE Initial Report Form has been sent (outcome, precise history, results of investigations, copy of hospital report, etc.) will be forwarded in a timely manner using the SAE Update Report Form (CCVTM form VC004F2). The Sponsor, or person with appropriate responsibility delegated from the Sponsor (Chief Investigator/medically qualified investigator), is responsible for commencing, maintaining and completing the SAE Sponsor Report Form (VC004F3). The anonymity of subjects shall be respected when forwarding this information.

SAEs which are not SUSARs will not normally be reported to the EC and MHRA, unless there is a clinically important increase in occurrence rate, an unexpected outcome, or a new event that is likely to affect safety of trial subjects.

In addition to these reporting requirements, the Investigator shall submit once a year throughout the trial, or on request, a safety report to the EC and MHRA (and a copy to the Sponsor).

We will follow every volunteer up for adverse event until their last visit. We will finish collection of AE data at the end of the trial, last volunteer last visit.

## **8.8 Reporting Procedures for SUSARs**

The Chief Investigator will report all SUSARs to the MHRA and ethical committee(s) within required timelines. The Chief Investigator will also inform all investigators concerned of relevant information about SUSARs that could adversely affect the safety of participants

If the SAE is a SUSAR it will be reported to the EC and MHRA within 7 days of the Chief Investigator having first knowledge of the event for fatal and life-threatening cases and within 15 days for all other SUSARs (and the report copied to the Sponsor). Any deaths occurring during the trial will be reported to the Sponsor. For all deaths, available autopsy reports will be made available for reporting to the regulatory authorities.

## **8.9 Local Safety Committee**

The local safety committee (LSC) will provide safety oversight for this trial. Its chair will be a clinician with extensive and relevant experience of infectious disease and clinical trials work. At the time of writing the chair is [name], Clinical Tutor in Medicine, Honorary Consultant Physician and Director of the Centre for Tropical Medicine at Oxford University. There will be a minimum of two other appropriately qualified committee members as specified in the site-specific SOP for safety reporting.

## **8.10 Development Safety Update report**

A development safety update report (DSUR) for each IMP is prepared annually, and submitted within 60 days of the anniversary of the first approval date from the regulatory authority for each IMP. This will be submitted by the chief Investigator to the competent authority and ethical committee(s).

## **8.11 Pregnancy**

Subjects who become pregnant during the trial after the vaccination may continue trial procedures including venepuncture, if appropriate, at the discretion of the Investigator. Subjects who become pregnant before MVA85A vaccination will be withdrawn and will not be vaccinated. Subjects who become pregnant between vaccination and bronchoscopy will not undergo bronchoscopy. The Investigator will collect pregnancy information on any subject who becomes pregnant while participating in this trial. The subject will be followed up to determine the outcome of the pregnancy.

# **9. STATISTICS**

## **9.1 Statistics**

This is primarily a trial with descriptive endpoints. Twelve subjects will be recruited into each arm of the trial (i.e. 36 in total). Our previous experience with clinical trials using MVA85A over the last 10 years suggests that this sample size is a feasible number to recruit, screen, enroll, and follow up in practical terms, whilst also allowing the determination of any substantial and clinically significant differences in safety and cell-mediated immunity between the three groups. A twofold increase in the magnitude of the cellular immune response (as measured by Elispot response to 85A peptide stimulation) is considered immunologically meaningful. Extrapolating effect size and variability from the completed initial aerosol vaccine safety study (TB026), twelve volunteers are needed to have 80% power to detect an immunologically meaningful difference in the summed peptide pools and 8

volunteers to achieve the same for single peptide pool of 85A. This sample size is appropriate for a proof-of-concept Phase I safety study.

It is anticipated that the immunological endpoints will not follow a normal distribution. A log transformation will be applied and if the resulting data are normally distributed they will be summarised by group using means and standard deviations. The one-week and six-month responses will be compared between the three groups using a t-test. If the resulting data are not normally distributed then medians and interquartile ranges will be used to summarise the data and the Mann Whitney U test will be used for statistical comparisons. An area-under-curve analysis will be used to compare the overall responses over time between the three groups. This analysis will make use of data collected at all time points.

Differences between means or medians between the three groups will be presented along with their 95% confidence intervals. Within each group, paired data will be analysed using either a paired t-test or the Wilcoxon matched pairs test depending on the normality of the data.

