## 2.2 Hypothesis

Previous studies have demonstrated that a 3 week interval between homologous MVA85A–MVA85A administered systemically does not enhance responses (8). We hypothesise that responses will be boosted in the aerosol–systemic and systemic-aerosol group but not in the systemic–systemic group.

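### The 80% power at twelve per arm in section 9.1 was not restated after v4.0 replaced the aerosol boost with placebo for some Group 2 volunteers, so it no longer holds for post-boost contrasts with the systemic-aerosol regimen

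*Protocol*

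**What the plan says.** **Sample size (protocol 9.1).** "Twelve subjects will be recruited into each arm of the trial (i.e. 36 in total"). The section defines the target: "A twofold increase in the magnitude of the cellular immune response (as measured by Elispot response to 85A peptide stimulation) is considered immunologically meaningful". The power claim is that "twelve volunteers are needed to have 80% power to detect an immunologically meaningful difference in the summed peptide pools". Eight suffice for a single pool. Both numbers are traced to the earlier aerosol study: "Extrapolating effect size and variability from the completed initial aerosol vaccine safety study (TB026"). The same paragraph presents the size as adequate for finding substantial differences in cell-mediated immunity between the three groups.

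**Planned comparisons (9.1).** "The one-week and six-month responses will be compared between the three groups using a t-test", with Mann-Whitney as the fallback, plus an area-under-curve comparison that uses every time point. Differences "will be presented along with their 95% confidence intervals".

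**Hypothesis (2.2).** "We hypothesise that responses will be boosted in the aerosol–systemic and systemic-aerosol group but not in the systemic–systemic group".

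**Group 2 after v4.0 (4.1 and the trial regimen in 6.1).** Volunteers whose day 28 boost falls on or after 2 September 2015 receive saline by both routes in place of the aerosol boost. Those who decline stay in follow-up with no vaccination or bronchoscopy. The day 0 prime is unchanged. Neither section says how many volunteers this affects.

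**The concern.** Section 9.1 makes twelve both the number needed and the number recruited, so there is no slack. The v4.0 change means that part of Group 2 never receives the systemic-aerosol regimen. That regimen is one of the two for which 2.2 predicts a boost. The power statement and the twelve-per-arm plan nevertheless stand as if all twelve received it.

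What is at stake is how a null result is read. If the systemic-aerosol regimen shows no clear post-boost difference from systemic-systemic, a reader of 9.1 will set that against an 80% assurance that no longer applies. An underpowered contrast could then pass for evidence that the boost does not work.

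**Working it through.** **Inputs from the protocol.** Twelve per arm, 80% power, twofold effect and a t-test on log-transformed data (all 9.1); placebo in place of the aerosol boost for part of Group 2 (4.1, 6.1).

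**Assumptions, because the protocol does not give them.** The twelve is per arm for a two-sample comparison. The test is two-sided at 5%, in line with the 95% confidence intervals. Group 3 has 12 evaluable volunteers. The SD is the one that makes the plan's own figure come out. The number k of aerosol-boosted Group 2 volunteers is unknown, so a range is shown.

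**Step 1: the plan's own figure.** It cannot be computed forward without an SD, so it is solved backwards. For n1 against n2, the noncentrality is d × √(n1·n2/(n1+n2)) with n1+n2−2 degrees of freedom, and power is the probability that this noncentral t exceeds the two-sided 5% critical value.
- With 12 against 12: √(144/24) = 2.449, 22 degrees of freedom, critical value 2.074.
- Power of 80% requires d = 1.197 (noncentrality 1.197 × 2.449 = 2.93).
- The implied log10 SD is log10(2)/d = 0.301/1.197 = 0.25.

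This takes the 80% as correct; it does not test it.

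**Step 2: the same effect and SD with k boosted against 12 in Group 3.** The detectable ratio is 10 to the power (d80 × 0.2515), where d80 is the standardised effect that gives 80% at that k.

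| k | √(12k/(12+k)) | Noncentrality | df | Critical t | Power for twofold | Ratio detectable at 80% |
|---|---|---|---|---|---|---|
| 12 | 2.449 | 2.93 | 22 | 2.074 | 80% | 2.0 |
| 11 | 2.396 | 2.87 | 21 | 2.080 | 78% | 2.03 |
| 10 | 2.335 | 2.80 | 20 | 2.086 | 76% | 2.08 |
| 8 | 2.191 | 2.62 | 18 | 2.101 | 70% | 2.19 |
| 6 | 2.000 | 2.39 | 16 | 2.120 | 61% | 2.37 |
| 3 | 1.549 | 1.85 | 13 | 2.160 | 40% | 3.11 |

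Every k below twelve is under 80%. That conclusion follows from the plan's own required number; the assumptions set only the size of the shortfall.

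**Step 3: which comparisons are touched.**
- Day 7, after the prime only: not affected, because the Group 2 prime is unchanged.
- One week after the boost (day 35) and six months: affected.
- Area under the curve: affected, because it includes the post-boost visits.

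**Step 4: keeping all twelve as randomised does not restore the figure.** Suppose placebo-boosted volunteers respond on average like Group 3 (an assumption). The Group 2 mean ratio then falls from 2 to 2^(k/12). With k = 6 that is 2^0.5 = 1.41, below the twofold target.

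**The case against.** **The trial is declared primarily descriptive, and safety is its primary objective.** True, and it keeps the point modest. But 9.1 goes on to state a formal power figure and name tests, so the figure should match the regimens now given.

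**Withdrawn subjects may be replaced (5.3).** This does not help here. Placebo-boosted volunteers remain in follow-up and are not withdrawn, and anyone entering Group 2 with a boost due after the cut-off date also receives placebo.

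**The number aerosol-boosted is not given, so the percentages are only scenarios.** This stands for the percentages. It does not stand for the direction: if v4.0 applies to even one of the twelve, the regimen falls short of the required number.

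**The SD, alpha and type of test may sit in the analysis plan.** Fair. Their absence is not the point made here.

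Stronger readings are tempting, but the documents do not support them:

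- *That 80% is wrong because the hypothesis needs both mixed-route arms to beat Group 3.* At d = 1.197 the joint power is about 69%. But 9.1 never promises joint or multiplicity-adjusted power, and 2.2 can equally be read as boosting within each group (0.8 × 0.8 = 64% if the two are independent). The 69% is a scenario and shows no error.
- *That between-group power is only 55% because twelve came from a paired calculation.* The word for increase in the twofold definition allows a paired reading, but the surrounding text favours twelve per arm and a between-group difference. Even on the paired reading, 55% needs change scores or a within-volunteer correlation of 0.5. For the planned test on responses, power runs from about 84% at zero correlation to 26% at 0.8.

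**Conclusion.** The point holds in limited form. After v4.0 the twelve-volunteer, 80% statement does not cover post-boost contrasts with the systemic-aerosol regimen, and 9.1 does not say so. Day 7 comparisons keep the stated figure.

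The shortfall depends on a number that the protocol does not give. It is trivial with 11 boosted (78%), modest with 10 (76%), and substantial with 6 (61%) or 3 (40%). These percentages rest on the assumptions listed in the working, above all on an SD back-solved from the plan's own 80%. The qualitative conclusion needs only that v4.0 applies to at least one of the twelve in Group 2.

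Nothing here shows that the sponsor's calculation was wrong for a single two-arm comparison with twelve evaluable volunteers in each arm.

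**What to change.** In section 9.1:

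1. Limit the 80% to a single between-group comparison with 12 evaluable volunteers in each arm.
2. Add a sentence that, after v4.0, fewer than twelve volunteers receive the systemic-aerosol regimen. Give the power, or the fold-difference detectable at 80%, for post-boost contrasts involving Group 2, using the number actually aerosol-boosted.
3. Compute that figure from the TB026 SD held by the sponsor. The 0.25 used here is back-solved and should not be copied into the protocol.
4. State that day 7 comparisons are not affected.

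The cost is a few sentences and one recalculation. One stated number becomes less favourable. There are no extra volunteers, no change to the design and no change to the regimens.
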